### Postoperative management

After surgery, all patients will be admitted to the postoperative care unit (PACU), where the PV analgesic infusion of 0.2% ropivacaine (0.1 L/kg/h) will be initiated. This PV analgesia will be maintained during the first 48 h after surgery. In the PACU, pain severity will be assessed at rest and during coughing using a numeric rating scale (0 = no pain, 10 = the worst imaginable pain). Furthermore, all patients will be provided with a patient-controlled analgesia pump (PCA) for the self-administration of PV rescue boluses of this solution during the first 48 h postoperatively. If the visual analogic scale (VAS) score is higher than 5 points, an intravenous bolus of 1 mg of morphine will be administered until the VAS reaches a value of less than 5 points.

We will record the number of PV boluses required and administered through the PCA pump within the first 48 h of the postoperative period. We will also record the morphine consumption during this period. Patients will be discharged from the PACU the following morning, except if the responsible physician considers that they should continue to have continuous surveillance.

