### Interventional treatment

Patients will be recruited consecutively and randomized into three groups of intraoperative management, as follows:
Group 1: Experimental arm—intravenous lidocaine and PV saline (SS). During intraoperative anesthetic maintenance, a continuous IV infusion of lidocaine at 1.5 mg/kg/h will be administered until the end of surgery, and perfusion of 0.9% SS will be administered through an intraoperative PV catheter at a rate of 0.1 mL/kg/h.Group 2: Experimental arm—intravenous SS and PV lidocaine. During anesthesia maintenance, a continuous intravenous infusion of 0.9% SS and an infusion of 2% lidocaine will be administered through an intraoperative PV catheter at a rate of 0.1 mL/kg/h.Group 3: Active comparator—intravenous remifentanil and PV SS. A continuous intravenous infusion of remifentanil will be administered at a rate of 0.1 mg/kg/min during anesthesia maintenance until the end of surgery, and an infusion of 0.9% SS will be administered through an intraoperative PV catheter at a rate of 0.1 mL/kg/ h.

The administration of the study drugs will be stopped immediately in cases where the study participant shows relevant deterioration (e.g., severe hypotension refractory to bolus dose vasoconstrictor treatment, or sudden life-threatening arrhythmia).

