### Induction and monitoring

Immediately before anesthetic induction, all patients will be monitored using electrocardiograms, pulse oximetry, and capnography. In addition, patients will be monitored using the bispectral index, cerebral oxygen saturation*,* invasive arterial pressure, and peripheral quantitative neuromuscular status. Regardless of the group assigned, all patients will be induced with 2 mg/kg of propofol, 3 μg/kg of fentanyl, and 0.6 mg/kg of rocuronium. Tracheal intubation will be performed with a double-lumen tube. Correct placement will be verified with a fiberoptic bronchoscope.

The patients will then be placed in the lateral decubitus position for the surgery. In this position, a PV catheter will be inserted into the hemithorax (level T5–T6) with a 3-mL initial test dose of 0.25% bupivacaine plus epinephrine (1:200.000), followed by continuous infusion of lidocaine or SS depending on the randomized group assignment. The assigned IV infusion treatment will be started at this time with PV infusion.

The parameters applied during ventilation will be different at three time points: 1) the baseline (BAS) parameters from orotracheal intubation until the initiation of OLV in two-lung ventilation (TLV) will be volume-controlled ventilation, a tidal volume (TV) of 8 mL/kg (ideal weight), positive end expiratory pressure (PEEP) of 5 cmH_2_O, FiO_2_ of 0.4–0.5, and respiratory rate to maintain an end-tidal carbon dioxide at 35 mmHg; 2) the values applied during OLV will be a TV of 6 mL/kg (ideal weight), ideal PEEP calculated as the one that provides the best lung compliance in the recruitment maneuver, permissive hypercapnia, and FiO_2_ of 0.6–1 to maintain SaO_2_ > 90%; and 3) for lung re-insufflation (END), the same ventilation parameters will be applied as in BAS. Recruitment maneuvers will be performed, and continuous positive airway pressure will be used in the nondependent lung when needed to resolve hypoxemia (SpO_2_ < 90%). Restrictive fluid therapy with crystalloids will be administered at 2 mL/kg/h to maintain diuresis > 0.5 mL/kg/h. A fluid bolus of 250 mL of crystalloids will be administered when diuresis is < 0.5 mL/kg/h.

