When closure of the thoracic incision begins, all the intervention infusions will be stopped, and a PV bolus of 0.15 mL/kg of 0.2% ropivacaine will be administered. The radial artery will be catheterized in all cases using the Pro AQT sensor to monitor the cardiac index, stroke volume variation, stroke volume index, and invasive arterial pressure. These values will be recorded at baseline during TLV, at 30 min after initiation of OLV, and at the end of OLV. Depending on the data recorded, vasoactive drugs will be administered to ensure optimal hemodynamic parameters for the intrapulmonary shunt. The respiratory parameters recorded during surgery will be as follows: TLV at baseline, 30 min after initiation of OLV, and the end of OLV, FiO_2_, SpO_2_, PaCO_2_, TV, minute volume, respiratory rate, peak pressure, plateau pressure, mean pressure, end expiratory pressure, lung dynamic compliance (Cdyn), and driving pressure.

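### The postoperative paravertebral ropivacaine rate is printed in litres per kg per hour, which the article's own figures rule out, and the IV infusions of groups 1 and 3 have two stop times

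*Protocol article*

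**What the plan says.** All figures are in the Protocol article.

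- **Postoperative PV infusion, all patients** (Postoperative management): "the PV analgesic infusion of 0.2% ropivacaine (0.1 L/kg/h) will be initiated". On duration: "This PV analgesia will be maintained during the first 48 h after surgery".
- **PV bolus of the same 0.2% solution, given as the chest is closed** (Induction and monitoring): "a PV bolus of 0.15 mL/kg of 0.2% ropivacaine will be administered".
- **Intraoperative PV infusions** (Interventional treatment): for group 1, "perfusion of 0.9% SS will be administered through an intraoperative PV catheter at a rate of 0.1 mL/kg/h"; for group 2, "an infusion of 2% lidocaine will be administered through an intraoperative PV catheter at a rate of 0.1 mL/kg/h". Group 3 receives PV saline at the same rate as group 1.
- **Fluid policy** (Intervention plan): restrictive crystalloid therapy, with a positive balance under 1.5 L in the first 24 h.
- **Stop time, first statement** (Interventional treatment): for group 3, "A continuous intravenous infusion of remifentanil will be administered at a rate of 0.1 mg/kg/min during anesthesia maintenance until the end of surgery". The IV lidocaine of group 1 has the same end point. No stop time is given there for group 2 or for any PV infusion.
- **Stop time, second statement** (Induction and monitoring): "When closure of the thoracic incision begins, all the intervention infusions will be stopped".

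**The concern.** The ropivacaine rate is the only PV quantity in the article expressed in litres. The others are in mL/kg/h, in mL/kg or, for the test dose, a fixed 3 mL. The infusion is given to every randomised patient for two days and is the background against which pain scores, patient-controlled boluses and morphine use are measured. A rate that cannot be delivered leaves that background undefined for anyone who reads, replicates or appraises the trial. Followed literally, it would be a safety matter.

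The stop times raise a different problem. The start of chest closure and the end of the operation are different events. A blinded anesthesiologist with a group 1 or group 3 patient is told to stop the IV infusion at both, so the end of exposure in those two arms is not fixed by the text.

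**Working it through.** The ropivacaine rate is a stated figure, with no derivation in the article to reproduce. The check is whether it can coexist with the other stated quantities. Body weight is not given, so 70 kg is assumed, with a range of 50 to 100 kg.

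**1. The rate as printed**
- Volume: 0.1 L/kg/h × 70 kg = 7 L/h (5 to 10 L/h).
- Drug: 0.2% is 2 mg/mL, so 100 mL/kg/h × 2 mg/mL = 200 mg/kg/h. At 70 kg this is 14,000 mg/h, or 14 g/h (10 to 20 g/h).
- Over 24 h: 7 × 24 = 168 L (120 to 240 L).
- Over 48 h: 7 × 48 = 336 L (240 to 480 L).

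**2. Against the bolus of the same solution**
- Bolus: 0.15 mL/kg × 70 kg = 10.5 mL (7.5 to 15 mL).
- One hour of infusion relative to one bolus: 100 ÷ 0.15 = about 667, whatever the body weight.
- Equivalently, the infusion would deliver a full bolus volume every 0.15 ÷ 100 h × 3600 = 5.4 seconds.

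**3. Against the fluid limit**
- 168 L ÷ 1.5 L = 112 (80 to 160). The limit concerns crystalloid management and net balance, so this shows scale and is not an exact breach. No allowance for output closes a gap of this size.

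**4. Against the scale of the intraoperative PV infusions**
- 0.1 mL/kg/h × 70 kg = 7 mL/h (5 to 10 mL/h).
- Ratio of the two printed rates: 100 mL/kg/h ÷ 0.1 mL/kg/h = 1000 exactly.
- These are different infusions in different periods, so the ratio supports the point but does not carry it. Steps 2 and 3 are enough alone.

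**5. Stop times side by side**

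| Infusion | Interventional treatment | Induction and monitoring |
|---|---|---|
| Group 1, IV lidocaine | End of operation | Start of chest closure |
| Group 3, IV remifentanil | End of operation | Start of chest closure |
| Group 2, IV saline and PV lidocaine | Not stated | Start of chest closure |
| Groups 1 and 3, PV saline | Not stated | Start of chest closure |

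The conflict is confined to the first two rows. The article gives no time between the two events, so the total difference in exposure cannot be computed. For group 1, each extra minute at 1.5 mg/kg/h adds 1.5 ÷ 60 = 0.025 mg/kg of lidocaine.

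**6. The remifentanil unit**
- As printed: 0.1 mg/kg/min × 70 kg × 60 min = 420 mg/h (300 to 600 mg/h).
- The article has no second remifentanil rate, concentration or total dose to set against this. The induction dose of "3 μg/kg of fentanyl" is another drug given once. It shows only that micrograms are used elsewhere for an opioid. Arithmetic cannot take this further.

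**The case against.** The best reply is that the ropivacaine figure is an evident slip in a condensed article. A rate that needs 336 L over two days cannot be delivered, the full protocol is not shown and may be correct, and nothing in the article suggests that any patient received the printed rate. The infusion is also common to all arms, so it leaves the randomised contrast, the primary outcome, the sample size and the analysis untouched. All of that stands, and it limits the reach of the point. It does not remove it: the article has not left a detail to another document but has stated a treatment figure that its own text rules out.

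On stop times, the rule in Induction and monitoring can be read as a more precise version of the looser phrase in Interventional treatment, and it applies to every arm. That reading is reasonable, but the article does not say which statement governs, and the two name different events.

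Three stronger readings are tempting, and the document does not support them:
- **That two values are given for one PV rate.** The intraoperative and postoperative infusions are separate treatments. The 100 mL PV supply in Randomization also belongs to the intraoperative period, so it does not test the postoperative rate.
- **That the remifentanil unit is a proven error.** No internal figure contradicts it, and milligram-per-kg doses are used elsewhere in the article for propofol, rocuronium and lidocaine.
- **That the stop-time conflict affects every arm.** It reaches only the IV infusions of groups 1 and 3.

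**Conclusion.** The ropivacaine rate must be corrected. As printed, one hour of infusion is about 667 times the article's own bolus of the same solution at any body weight, and 24 h of it is 80 to 160 times the stated fluid limit for patients of 50 to 100 kg. The bolus comparison needs no assumption; the litre figures rest on the assumed weights. What is affected is the stated background analgesia of every patient. The definition of the comparator and the validity of the between-arm comparison are not.

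The stop-time conflict is real but smaller. It concerns two IV infusions, and its size in minutes is unknown. The remifentanil unit remains a query and is no part of the demonstrated contradiction.

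**What to change.** Reconcile Interventional treatment, Induction and monitoring, and Postoperative management against approved protocol version 4.0. Then:

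- publish a correction of the ropivacaine rate and its unit, as version 4.0 has it;
- state a single stop time for the study infusions and use it in both sections;
- while the source is open, verify the remifentanil unit and either confirm or correct it.

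If version 4.0 contains the same inconsistencies, they need to be resolved there first by those responsible for the clinical protocol. Which rate, unit or stop time is right is not for this review to say. The cost is a document check and a short published correction. Sample size, randomisation and analysis do not change.

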#### Outcomes

##### Primary outcome

The primary outcome is the proportion of patients included in the different scales of the Clavien–Dindo (C–D) classification [20] in the three groups of patients. The greater the intensity of the treatment that is necessary to correct any postoperative complication, the higher the C–D classification will be considered. Any deviation from a normal postoperative course will be classified into grade I, II (minor complications), IIIa, IIIb, IVa, IVb, and V (major complications) of this classification (Appendix 1).

##### Secondary outcomes

Secondary objectives including the following will be the comparison between three groups of patients with the following laboratory or clinical data:

Secondary clinical outcomes
Postoperative pain intensity: Postoperative pain will be evaluated using the VAS at rest, during movement, and when coughing during the stay in the PACU and in the two days after. We will also record the doses of self-administered rescue analgesics by PCA pump during the first 48 h after surgery, as well as the cumulative morphine consumption in the first 48 h post-operation.Postoperative pulmonary complications (PPCs): PPCs will be classified using the definition applied in the ARISCAT study [21] (atelectasis, suspected pulmonary infection, respiratory failure, bronchospasm, aspiration pneumonitis, pleural effusion, and pneumothorax; Appendix 2). Because pneumothorax and pleural effusion are the usual outcomes after LRS in the nondependent lung, we will consider them to be complications only if they occur in the dependent lung. The time frame is up to 30 days after intervention.Postoperative cognitive dysfunction (POCD) is defined as the presence of a mini-mental test value less than 27 points at 3 days postoperative (in patients with a value of 30 points on preoperative mini-mental test) or if there is a drop of more than 3 points compared to the value obtained preoperatively (in patients with a mini-mental preoperative test value less than 30 points).The incidence of postoperative surgical complications, which is defined as the presence of any of the complications during the first 30 days postoperatively, as follows:
◦ Wound infection: Infection of the incisional surgical site, purulent drainage and/or isolation of pathogenic microorganisms◦ Prolonged air leak: Air escape through the thoracic drainage tubes beyond postoperative day 5◦ Bleeding: A surgical wound that requires re-intervention or the patient requires transfusion of blood products◦ Subcutaneous emphysema: Palpation of subcutaneous crepitation or the presence of subcutaneous air in a thoracic image (chest X-ray or computed tomography)◦ Bronchopleural fistula: Communication of the bronchus with the pleural space as shown on a thoracic image◦ Pleural empyema: Pleural effusion with the macroscopic presence of pus, a positive Gram stain or culture of pleural fluid, or a pleural fluid pH under 7.2 with normal peripheral blood pH◦ Cardiac herniation: Presence of the heart outside its expected position, as shown on a thoracic image◦ Surgical re-intervention: Patient who requires reoperation for any reason (pulmonary or not)Incidence of postoperative cardiac complications within 30 days postoperatively, if any of the following cardiac events occur:
◦ Cardiac arrhythmias: defined as evidence of an abnormal heart rhythm electrocardiograph (ECG) that was not present before the intervention◦ Stroke episodes: defined as an acute focal injury of the central nervous system that has a vascular cause (embolic, thrombotic or hemorrhagic) with residual motor deficit, sensory, or cognitive dysfunction◦ Cardiac failure: The presence of new respiratory distress, S3, jugular venous distension, and a new chest X-ray finding of pulmonary vascular redistribution or interstitial◦ Myocardial ischemia: An increase in ultrasensitive troponin with at least one value above the 99th percentile of the upper reference limit and at least one of the following criteria: ECG changes compared to preoperative ECG that suggests ischemia or new echocardiographic (wall motion) abnormalities◦ Cardiac arrestIncidence of postoperative renal complications.Postoperative acute kidney failure is defined as an increase of serum creatinine more than 1.5 times or ≥ 0.3 mg/dL from baseline or urine output < 0.5 mL/kg/h for 6 h using the acute kidney injury network (AKIN) classification [22]. Time frame: up to 30 days after intervention.Length of stay in the hospital and PACUUnplanned readmissions to the hospital and PACU during the first 30 postoperative days

Secondary laboratory outcomes:
Systemic inflammatory biomarkers (IL-1, IL-2, IL-6, IL-8, IL-10, TNF-α, and monocyte chemoattractant protein) in serum and BAL fluid. Neuroinflammatory markers (S-100 beta protein, neuronal specific enolase, and glial fibrillary acidic protein) measured in serum during the first 24 h postoperativelyThe gas exchange: measured as PaO_2_/FiO_2_ at 24 h after the intervention

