**Fig. 1 Fig1:**
[figure not shown]
Consort list

At the preoperative visit, a member of the research team will visit the candidate to explain the study. If a patient agrees to be included in the study, they will be asked to sign an informed consent form and undergo a mini-mental state examination. No anxiolytics will be administered to the patients before the surgery.

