### Randomization

Patients will be randomized into the following three groups (1:1:1 ratio): intravenous lidocaine and PV saline (group 1); IV and PV saline solution with lidocaine (group 2); or IV remifentanyl and PV saline solution (group 3). The randomization will be performed using the software EPIDAT 3.1 before the first patient is recruited, and the randomization codes will be kept in a sealed envelope with a number on the outside of the envelope.

A study nurse will be in charge of preparing the medication according to the result obtained in the envelope. The surgical anesthesiologist will receive the assigned and prepared medication for the corresponding group with only the identification of IV perfusion (500 mL) and PV perfusion (100 mL) without knowledge of the group to which the patient belongs. The content of solutions will be indistinguishable to the investigating team because all of the solutions are clear liquids.

For bias control, the physicians involved will be blinded to the techniques used, including the anesthesiologist responsible for the intraoperative management of the patient, the physician responsible for postoperative control in the postoperative care unit, and the guard physician who will perform the cognitive dysfunction test preoperatively and postoperatively, as well as the follow up until the month of surgery. Those responsible for analysis of the biological samples will also be blinded.

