### Power calculation

The primary outcome of this clinical trial is the comparison of the proportion of patients included in the different C–D classifications, which indicate the severity of postoperative complications for thoracic surgery. Two comparisons are planned: IV lidocaine + SS-PV vs remifentanyl IV+ SS-PV, and lidocaine PV + SS-IV vs remifentanyl IV+ SS-PV. The sample size is calculated based on the C–D classification ordinal scale. According to a similar study design by our research group, the standard deviation of this scale is approximately 1.5 units. Thus, it is necessary to include 48 patients per group with an alpha risk of 5% and a beta risk of 10% in a two-tailed comparison to detect differences ≥ 1 unit. Because losses are estimated to be 5%, the final sample size should be at least 153 patients (sample size calculator GRANMO version 7.12 April 2012).

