#### Statistical analysis

Descriptive statistics (mean (standard deviation; SD) or median (IQ25–75)) will be used for continuous variables. Normality will be assessed using the Kolmogorov–Smirnov test. When the variables have a normal distribution, ANOVA and a post hoc Bonferroni test will be applied. If the variables do not have a normal distribution, a non-parametric test will be used to compare them. In this case, the Kruskal–Wallis test and Mann–Whitney test will be used to make post hoc comparisons.

A one-way repeated-measures ANOVA will be performed to analyze repeated measurements of continuous variables. Categorical variables will be presented as absolute frequencies and percentages and compared between groups using the Pearson chi-squared test or Fisher exact test. The odds ratio will be calculated with the 95% confidence interval for categorical postoperative outcome variables. The statistical analyses will be performed using SPSS version 21.0. Statistical significance is set at *p* < 0.05.

Before the digitization and statistical analyses, an investigator will review the data record form for completeness and correctness. At this time, missing data will be identified, drawn from source data, and filled into the case record forms if possible. We do not expect to obtain missing data with outcome variables because they are recorded in a mandatory manner in the electronic hospital files. However, missing pre- or intraoperative data will be treated with a regression imputation method. Data will be analyzed according to the intention-to-treat principle.

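### Cognition is tested only as a yes/no fall of 4 or more mini-mental points; a baseline-adjusted comparison of the day-3 score should be added beside it

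*Protocol article*

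**What the plan says.** The mini-mental is given twice. Under Intervention plan, consenting patients will "undergo a mini-mental state examination" before surgery, and the visit table in Appendix 3 marks the test on day -1 and day 3. The Randomization section lists "the guard physician who will perform the cognitive dysfunction test preoperatively and postoperatively" among the blinded staff.

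Secondary outcomes turns these two scores into one event. For a patient with a preoperative score of 30, POCD "is defined as the presence of a mini-mental test value less than 27 points at 3 days postoperative". For a patient below 30, it is recorded "if there is a drop of more than 3 points compared to the value obtained preoperatively". No other outcome based on the test is defined.

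Under Statistical analysis, categorical variables are "compared between groups using the Pearson chi-squared test or Fisher exact test", with an odds ratio and 95% confidence interval for postoperative outcomes. The same section gives general rules for continuous and repeated measurements, but nothing in the article lists the mini-mental score as such a variable.

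Power calculation concerns the Clavien-Dindo scale only. No event rate, SD or power is given for cognition.

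**The concern.** Cutting a 30-point scale at one value discards most of what it records. A fall of 1, 2 or 3 points counts as no change, and a fall of 4 counts the same as a fall of 12.

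This matters most if the treatment shifts many patients a little, which the article's own rationale makes plausible. Background links inflammation to postoperative cognitive dysfunction, and the trial's hypothesis is that lidocaine dampens the systemic inflammatory response. A modest shift spread over many patients would mostly stay below the cut. With arms sized for a different endpoint, it would probably be reported as no difference in POCD and read as no difference in cognition, although the collected scores could show more.

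**Working it through.** **1. The plan's own figure.** Power calculation gives a detectable difference of 1 unit and says that "the standard deviation of this scale is approximately 1.5 units". With two-sided 5% and 90% power:

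n = 2 × (1.960 + 1.282)² × 1.5² / 1² = 47.3, so 48 per group.

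48 / 0.95 = 50.5, so 51 per group, and 3 × 51 = 153. Both stated figures reproduce. The 48 per arm is used below as the analysable number.

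**2. The two branches are one rule.** From a baseline of 30, a score below 27 means 26 or less, a fall of at least 4. From a lower baseline, a fall of more than 3 on an integer scale is also at least 4. Checking each baseline from 24 to 30 gives the same result.

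**3. One case by hand.** All cognitive inputs from here on are assumptions. Take a mean decline of 1 point in one arm and 0 in the other, with SD of change 2. With the cut placed at 3.5:

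- POCD rates: 1 − Φ((3.5 − 1)/2) = 1 − Φ(1.25) = 10.6%, and 1 − Φ((3.5 − 0)/2) = 1 − Φ(1.75) = 4.0%.
- Yes/no outcome: the difference is 0.0656, the pooled standard error √(2 × 0.0729 × 0.9271/48) = 0.0531 and the unpooled one 0.0526. Power = Φ((0.0656 − 1.96 × 0.0531)/0.0526) = Φ(−0.73) = 23%.
- Score: power = Φ(1/(2 × √(2/48)) − 1.96) = Φ(0.49) = 69%.
- For 90% power the cut needs 328 per arm and the score 85.

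This ignores the ceiling at 30. Simulated with integer scores and the ceiling, the same case gives about 25% against 61%.

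**4. General shift, simulated.** 48 per arm; baseline N(28, 1.7), rounded and capped at 30; day-3 score = baseline minus change, rounded and capped at 30; two-sided 5%; 3,000 replicates.

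| Mean drop, arm A vs B | SD of change | Chi-squared on POCD | Day-3 score adjusted for baseline | Mann-Whitney on change |
|---|---|---|---|---|
| 1.5 vs 0.5 | 2 | 32% | 66% | 64% |
| 2 vs 1 | 2 | 35% | 64% | 63% |
| 2 vs 1 | 2.5 | 30% | 48% | 46% |
| 1.5 vs 0.5 | 2.5 | 26% | 45% | 44% |
| 2.5 vs 1 | 2.5 | 55% | 79% | 77% |
| 2 vs 0.5 | 2.5 | 52% | 80% | 78% |
| 3 vs 1.5 | 2.5 | 59% | 80% | 80% |

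Repeating the simulation moves single cells by up to about 4 points; the cut in the last row ranged from 59% to 63%. The fair summary is about 26-61% for the cut against about 45-80% for the adjusted score. The rank test does nearly as well as the model here, so the gain comes from using the whole scale and not from covariate adjustment. With SD 3 and a 1-point shift (1 vs 0), the figures fall to about 19% and 32%.

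**5. Effect confined to some patients, simulated.** Same baseline; only a share of each arm declines, and the rest show noise.

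| Share declining, A vs B | Mean drop | Noise SD | Chi-squared on POCD | Adjusted score | Mann-Whitney |
|---|---|---|---|---|---|
| 25% vs 5% | 6 | 1 | 83% | 71% | 42% |
| 25% vs 5% | 6 | 1.5 | 79% | 65% | 41% |
| 25% vs 5% | 5 | 1.5 | 71% | 58% | 40% |
| 30% vs 10% | 7 (SD 3) | 1 | 65% | 58% | 39% |

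Here the cut wins: by 7 to 14 points over the adjusted score (79 − 65 = 14 at most) and by 26 to 41 over the rank test. With milder drops of about 3 points (30% vs 10% declining) the two are close: the adjusted score ranged from 3 points worse to about 6 better, depending on the exact set-up.

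**The case against.** The strongest objection is that the article does not ask about a general difference in cognition. It asks about POCD, listed with pulmonary, surgical, cardiac and renal complications that are all counted as events. Incidence is the natural quantity for a complication. A vulnerable minority with large drops is the pattern such a definition describes, and step 5 shows the cut doing better there. This stands, and it rules out a stronger reading that a reader might take from step 4: that the score should replace POCD as the test, at a trivial cost in power. Replacement would change the question, and the loss can reach about 14 points.

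Two further inferences are not supported. The article cites sources for Clavien-Dindo, ARISCAT and AKIN but none for the POCD cut; in a condensed article this does not show that the cut is unsound. Nor does its silence show that a score analysis is ruled out, since an analysis plan that is not shown may contain one. What can be said is that the outcome as fixed here is binary and no score comparison is named.

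It is also fair that this is one of many secondary outcomes without their own power calculation. The adjusted score itself reaches only about 45-66% for a 1-point shift at SD 2 to 2.5, so a null score result would not be conclusive either. The confidence interval would at least show what had been excluded.

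**Conclusion.** The point holds as a minor one. The cognitive outcome is a single cut at a fall of 4 points. For a general difference of 1 to 1.5 points it has about 26-61% power, against about 45-80% for the baseline-adjusted score. These figures assume 48 per arm, the stated baseline distribution and an SD of change of 2 to 2.5, none of which the article gives for the mini-mental except the arm size. The direction held in every general-shift scenario tried, but the gap narrows as the SD grows and reverses when a few patients have large drops.

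Neither analysis is better for every shape of effect, and the shape is unknown. That supports having both, not exchanging one for the other. The primary outcome and the sample size of 153 are unaffected.

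**What to change.** Keep the POCD comparison and its odds ratio as the complication outcome. Add one pre-specified sentence to the analysis: the day-3 mini-mental score is compared between arms in a linear model with the preoperative score as covariate, reporting the mean difference and 95% confidence interval for each lidocaine arm against remifentanil. State that a null POCD result will be interpreted together with that interval.

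The linear model is preferable to a rank test on change: it performs about the same under a general shift and loses much less when the effect sits in a few patients.

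Cost: one more secondary comparison, and a mean difference that is clinically less direct than a POCD rate. No new data, visits or patients are needed.
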